### Secondary aims

The secondary aims of this study are as follow:
To determine the effects of vitamin D supplementation on the status of oxidative stress in asthenospermia infertile men with vitamin D deficiencyTo determine the effects of vitamin D supplementation on endocrine factors involved in fertility in asthenospermia infertile men with vitamin D deficiency

### Practical aims

Vitamin D supplementation will be recommended for asthenospermia infertile men, if its beneficial effects would be confirmed in this study. Also, in order to increase dietary intakes of vitamin D in infertile men, there will be necessary recommendations provided for these patients.

### Primary outcomes

The primary outcomes are as follow:
Changes in the mean serum levels of 25-OHD between and within two groups pre and post intervention in asthenospermia infertile menChanges in the mean ejaculation volume, total sperm count, percentage of motile sperm, number of sperm with normal morphology, number of live sperm in semen between and within two groups pre and post intervention in asthenospermia infertile men.

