## Methods/design

### Study subjects

This trial will be conducted on 86 infertile men with idiopathic asthenozoospermia (the mobility of sperm < 40% and rapid progressive sperm motility < 32% [50], and with serum vitamin D levels < 30 ng / ml, who report inability to have a child after at least 1 y of marriage without using any preventive methods and with normal fertile female partner in the Infertility Clinic of Ahvaz Jahad daneshgahi, Iran. The further inclusion criteria are listed in Table 1.

**Table 1 Tab1:** Inclusion and exclusion criteria

Inclusion	
•Men aged 20 to 50 years	
•Idiopathic asthenozoospermia (the mobility of sperm < 40% and rapid progressive sperm motility < 32%	
•Serum vitamin D levels < 30 ng / ml	
•Access to the infertility clinic of Ahvaz Jahad daneshgahi, Iran	
•Inability to have a child after at least 1 y of marriage without using any preventive methods	
•Normal fertile female partner	
•No history (≤ 12 weeks) of medical therapy	
•Not having a history of epididymo-orchitis, prostatitis, genital trauma, testicular torsion, inguinal or genital surgery, urinary tract infection, or previous hormonal therapy, another genital disease (cryptorchidism, current genital inflammation or varicocele), a recent history of sexually transmitted infection, hepatobiliary disease and renal insufficiency, severe general or central nervous system disease and endocrinopathy, using cytotoxic medications, immunosuppressant, anticonvulsants, androgens, antiandrogens	
•No smoking, drug or alcohol abuse, and	
•No occupational and environmental exposure to possible reproductive toxins	
•Body mass index of < 30 kg/m^2^	
Exclusion	
• Have any acute illness	
• Use less than 90% of the prescript supplement	
• Would like to leave the study personally	
• Participate in another study	
• Immigrate	
• Not available for following-up	

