### Sample size

The sample size was calculated based on the progressive sperm ratio as the primary variable [29]. Considering a type I error of 0.05 and 90% for the power study, 34 patients were determined for each group. Also, regarding with the attrition rate of 25%, 43 patients will be included for each group. The formula used for the sample size was as follow:
$$ n=\frac{{\left({z}_1-\frac{\alpha }{2}+{z}_1-\beta \right)}^2\left({\delta_1}^2+{\delta_2}^2\right)}{{\left({\mu}_1-{\mu}_2\right)}^2} $$

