### Statistical analysis

Intention-to-treat (ITT) and per-protocol (PP) populations will be used in the analysis. The ITT population consists of all individuals who will be randomized, whereas the PP population consists of all participants who complete the 12-week intervention. All data will be analyzed using SPSS (Version 22; SPSS Inc., Chicago, IL). Results will be expressed as mean ± SD and frequency and (percentage) for quantitative and qualitative variables respectively. The normal distribution of variables will be tested and confirmed by Kolmogorov-Smirnov test. The baseline differences of mean values between groups will be tested using independent sample t-test or Mann-Whitney U test for normal and non- normal distribution variables respectively. Analysis of covariance (ANCOVA) will be used to identify any differences between the two groups at the end of study, adjusting for baseline values and covariates (such as BMI, age, dietary intake including dietary calorie, calcium, F, selenium, vitamin C, E, A, D and zinc, physical activity, sun exposure, season, serum vitamin d, PTH and calcium). The comparison of mean values within groups pre- and post-intervention will be done by paired sample t tests and Wilcoxon signed-rank test as nonparametric alternatives for normal and non- normal distribution variables respectively. Differences will be considered statistically significant at *P* < 0.05.

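### The trial is sized on the progressive sperm ratio as its primary variable, but the Primary outcomes list omits it and names six other outcomes, all tested at 0.05 without ranking

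*Protocol article*

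**What the plan says.** Five places in the protocol article bear on this.

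- **Sample size:** "The sample size was calculated based on the progressive sperm ratio as the primary variable". The section continues: "Considering a type I error of 0.05 and 90% for the power study, 34 patients were determined for each group". The number is then raised to 43 per group for attrition, 86 in total.
- **Primary outcomes:** six outcomes, each compared both between and within groups. The first is serum 25-OHD. The other five are "mean ejaculation volume, total sperm count, percentage of motile sperm, number of sperm with normal morphology, number of live sperm in semen". Progressive motility is not among them, and it is not in Secondary outcomes either.
- **Study subjects, Table 1 and Semen and blood samples:** sperm mobility and rapid progressive motility have separate cut-offs, 40% and 32%.
- **Statistical analysis:** "Differences will be considered statistically significant at *P* < 0.05". No outcome is ranked above another, and no co-primary rule or adjustment is given.
- **Practical aims:** "Vitamin D supplementation will be recommended for asthenospermia infertile men, if its beneficial effects would be confirmed in this study". The outcome that would do the confirming is not named.

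**The concern.** A trial's error rate and power describe one specified comparison. Here the comparison that was powered is not on the list of primary outcomes, and none of the comparisons on that list was powered. A reader of the final report could not tell which result decides the trial.

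The list then offers five semen outcomes, each at 0.05, with nothing to say which counts. A favourable chance result on any one of them could be presented as a met primary outcome, and Practical aims would let it support a recommendation. 25-OHD adds a second route. Participants enter with levels below 30 ng/ml and the active arm takes vitamin D3, so a rise is the expected effect of taking the supplement. As a primary outcome it could be met with no benefit in semen quality.

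**Working it through.** **1. The plan's own sample size**

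Inputs from Sample size: type I error 0.05, two-sided because the printed formula uses α/2; power 90%; 34 per group.

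Formula: n = (z₁₋α/₂ + z₁₋β)² (σ₁² + σ₂²) / (μ₁ − μ₂)².

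No means or SDs are printed, so 34 cannot be rebuilt forward. Inverting the formula with equal SDs gives the standardised difference it implies:

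d = √[2(1.960 + 1.282)² / 34] = √(21.01 / 34) = 0.786.

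Any d from 0.786 up to just under 0.798 rounds up to 34. This is a back-calculation, not a figure from the article, and it concerns the progressive sperm ratio only. No effect size or SD is given for any of the six listed outcomes, so their power cannot be computed.

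The 43 per group matches 34 × 1.25 = 42.5, rounded up.

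**2. Is the sizing variable on the list under another name?**

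| Section | Variable named |
|---|---|
| Sample size | progressive sperm ratio |
| Primary outcomes (nearest item) | percentage of motile sperm |
| Study subjects, Table 1 | sperm mobility (< 40%) and, separately, rapid progressive motility (< 32%) |
| Semen and blood samples | motility grade, with the same two cut-offs again |

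The article gives overall mobility and rapid progressive motility different thresholds, so it treats them as different quantities. The percentage of motile sperm therefore cannot simply be read as the progressive ratio.

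**3. False-positive chance across the five semen outcomes**

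25-OHD is left out of the count. If the supplement is expected to raise it, its null hypothesis is expected to be false and it cannot give a false positive. The within-group comparisons are also left out.

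For five independent between-group tests at 0.05: 1 − 0.95⁵ = 0.226.

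The article gives no correlations between outcomes. Assuming test statistics that are multivariate normal with equal pairwise correlation ρ, the chance that at least one exceeds 1.960 in absolute value is:

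| ρ (assumed) | At least one false positive |
|---|---|
| 0 | 22.6% |
| 0.3 | 20.9% |
| 0.5 | 18.3% |
| 0.7 | 14.8% |
| 0.9 | 10.2% |

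Against 5%, the ratio runs from 10.2 / 5 ≈ 2.0 to 22.6 / 5 ≈ 4.5.

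**The case against.** **The sizing variable is declared primary.** A reader might infer that the 90% power belongs to no primary comparison at all. The text does not support that: Sample size expressly calls the progressive sperm ratio the primary variable. The defect is a conflict between two sections.

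**All six outcomes might be counted.** Six independent tests would give 1 − 0.95⁶ = 26.5%. That figure cannot be used alongside the argument that 25-OHD is expected to rise, so only the five semen outcomes are counted.

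**The semen measures are probably well correlated.** Three of the five are counts from the same ejaculate, so the independent figure is best read as an upper value. This stands. Even at an assumed correlation of 0.9, the chance is about twice the nominal rate.

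**Bonferroni might be said to ruin the power.** At 0.05/6 with 34 per group and d = 0.786, power is about 73%. That rests on the back-calculated effect, applies it to outcomes for which no effect is stated, and ignores the planned baseline-adjusted ANCOVA. If 0.786 is scaled to the unadjusted SD and the baseline correlation is 0.5 (both assumed), it is about 86%. The case for a single primary outcome does not depend on either figure.

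**A separate analysis plan may deal with multiplicity.** It may, and the 0.05 sentence does not prove that no adjustment is intended. Such a plan would not remove the mismatch between Primary outcomes and Sample size, which is the firmer part of the point.

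**25-OHD already has an intermediate role.** Primary aim presents raising it as a step towards evaluating fertility. That supports calling it a treatment check, but Primary outcomes still lists it first. The article gives no figure for how likely a rise is, so the claim here is only that a rise is expected.

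**Conclusion.** The point holds as a contradiction within the article that must be resolved before unblinding. Sample size and Primary outcomes name different primary variables, and the stated 90% power applies to none of the six listed outcomes. This rests on the text alone.

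The size of the multiplicity problem depends on assumptions. With five semen outcomes at 0.05 and no true effect on any of them, the chance of at least one false positive lies between about 10% (equal correlation 0.9) and 22.6% (independence), roughly two to four times the nominal 5%. It also assumes that no adjustment is made elsewhere.

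**What to change.** Make these changes before the codes are opened:

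1. Define the progressive sperm ratio as one measured quantity, and reconcile it with the rapid progressive motility of Table 1 and the motility grade of Semen and blood samples.
2. Name its between-group difference at week 12 as the single primary outcome: ITT population, ANCOVA adjusted for baseline, two-sided 0.05.
3. Reclassify 25-OHD as a treatment-check outcome.
4. Make the other semen parameters secondary, either Holm-adjusted or labelled exploratory.
5. State in Practical aims that benefit counts as confirmed only on the single primary outcome.
6. Record this as a dated amendment with its reasons, and update the registry entry if it differs. That entry was not available for this review.

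The planned 86 men do not change. Motility grade is already collected, and the ITT population and baseline-adjusted ANCOVA are already in Statistical analysis. The change brings the stated 5% error and the planned basis for power back to the outcome that decides the trial.

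The cost is more than wording. Recruitment began in April 2018 and was predicted to end in September 2021, so primary outcomes would be redesignated about three years into enrolment. That needs a written justification and ethics review, and is credible only while the trial remains blinded. The other listed outcomes also lose confirmatory status.

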### Secondary outcomes

Secondary outcomes are:
Changes in the mean serum and seminal levels of MDA (Malondialdehyde), 8-hydroxy-2- Dioxy Guanosine (8-OHDG), total antioxidant capacity (TAC), and sperm DNA fragmentation index (DFI) between and within two groups pre and post intervention in asthenospermia infertile menChanges in the mean serum levels of luteinizing hormone (LH), follicle-stimulating hormone (FSH), total testosterone (T), estradiol (E2), sex hormone-binding globulin (SHBG), free androgen index (FAI = T/SHBG. 100), T/LH and T/E2 ratios, prolactin (PRO), parathyroid hormone (PTH), osteocalcin (OCN) between and within two groups pre and post intervention in asthenospermia infertile men.Changes in the mean serum and seminal levels of calcium and serum phosphorus between and within two groups, pre and post intervention in asthenospermia infertile men.

### Supplements

The vitamin D3 supplements and placebo (containing maltodextrin) will be supplied by the “Pharmaceutical Technology Development Center of Ahvaz Jundishapur University of Medical Sciences, Iran”.

### Ethical considerations and trial registration

The protocol of this study was approved by the “Medical Ethics Committee of Ahvaz Jundishapur University of Medical Sciences” (approval no.: IR.AJUMS.REC.1396.1013) considering its accordance with the Declaration of Helsinki and was also registered at “Clinical Trials Registry of Iran” (IRCT20151128025274N4). A written consent will be obtained from all patients before starting the study. All patients’ data will be held confidential. This study will be financially supported by the Vice-Chancellor for Research Affairs of Jundishapur University of Medical Sciences, Ahvaz, Iran.

### Sample size

The sample size was calculated based on the progressive sperm ratio as the primary variable [29]. Considering a type I error of 0.05 and 90% for the power study, 34 patients were determined for each group. Also, regarding with the attrition rate of 25%, 43 patients will be included for each group. The formula used for the sample size was as follow:
$$ n=\frac{{\left({z}_1-\frac{\alpha }{2}+{z}_1-\beta \right)}^2\left({\delta_1}^2+{\delta_2}^2\right)}{{\left({\mu}_1-{\mu}_2\right)}^2} $$

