### Primary aim

The primary aim of the present study is to improve serum levels of 25OHD3 through vitamin D3 supplementation in order to evaluate its effects on fertility in infertile men. The compliance of subjects will be monitored by counting the remaining supplements. The subjects who may not use greater than 90% of the supplements will be excluded. We expect that the drop-out rates will be high in this study. Therefore, we would consider a 25% attrition rate for each group of study.

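### The stated 90% power belongs to 34 completers per group; it is not shown for the intention-to-treat comparison of all 86 randomised men

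*Protocol article*

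**What the plan says.** The Sample size section takes progressive sperm motility as the sizing variable, with the effect drawn from a cited trial, and prints the usual two-means formula. It reports: "Considering a type I error of 0.05 and 90% for the power study, 34 patients were determined for each group". It then adds that "regarding with the attrition rate of 25%, 43 patients will be included for each group", which makes 86 in all.

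The Statistical analysis section names two populations: "Intention-to-treat (ITT) and per-protocol (PP) populations will be used in the analysis". It defines them as follows: "The ITT population consists of all individuals who will be randomized, whereas the PP population consists of all participants who complete the 12-week intervention". Neither is called primary.

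The Primary aim section has a rule on intake: "The subjects who may not use greater than 90% of the supplements will be excluded". It goes on to expect high drop-out and concludes: "Therefore, we would consider a 25% attrition rate for each group of study". The Withdrawal of participants section puts low intake, acute illness and joining another study on the same list as leaving, emigrating and being unavailable for follow-up. The Discussion describes the 25% as withdrawal and drop-out.

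**The concern.** The sizing step treats the 25% as absent from the analysis, whereas the ITT definition keeps every randomised man. Part of the 25% may be men who took too little supplement or fell ill, and such men could still give a week-12 sample. If they are analysed as randomised, the expected mean difference shrinks. The nine men per group added for attrition replace numbers; they do not restore the difference. The single 90% is given with no population attached.

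This matters for how the result is read. The Practical aims section ties a recommendation on supplementation to this trial. A reader who takes 90% as the power of the ITT comparison could over-read a non-significant ITT result as absence of effect. The same reader could prefer a significant PP result because it looks like the properly powered one, although the PP set is selected after randomisation.

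**Working it through.** **Inputs.** From Sample size: type I error 0.05 (two-sided, from the 1 − α/2 term in the formula), power 90%, 34 per group, 25% attrition, 43 per group randomised. Not given: the means and SDs, the effect assumed in non-completers, the baseline correlation, and how missing outcomes enter ITT.

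**Step 1: the plan's own figure.** The 34 cannot be computed forwards without means and SDs, so it is solved backwards with equal SDs:

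d = (1.960 + 1.282) × √(2/34) = 0.786.

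Putting d = 0.786 back into the formula returns 34 per group and 90.0% power, which is consistent by construction. Because 34 may be a rounded-up figure, d could be as high as 0.798.

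**Step 2: the attrition step.** 34 × 1.25 = 42.5, rounded up to 43. If 25% of 43 are lost, 43 × 0.75 = 32.25 remain, which is fewer than 34.

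**Step 3: power for the possible fates of the 25%.** By normal approximation, power = Φ(δ × √(n/2) − 1.960), where n is the number analysed per group and δ the average standardised difference. If all 43 are measured and non-completers keep a fraction k of the benefit, δ = 0.786 × [0.75 + 0.25k].

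| Fate of the 25% | n per group | δ | Power |
|---|---|---|---|
| All lost, no outcomes (PP or ITT) | 32.25 | 0.786 | 88.4% |
| All measured, no benefit (k = 0) | 43 | 0.590 | 78.1% |
| Half measured with no benefit, half lost | 37.6 | 0.674 | 83.2% |
| All measured, half the benefit kept (k = 0.5) | 43 | 0.688 | 89.1% |
| All measured, k = 0.75 | 43 | 0.737 | 92.8% |

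**Step 4: where 90% is regained.** With 43 measured per group, 90% needs δ/0.786 = √(34/43) = 0.889. Setting 0.75 + 0.25k = 0.889 gives k of about 0.56. Above that, ITT has 90% or more.

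**Step 5: sensitivity of the lowest figure.** The noncentral t gives 77.1% in place of 78.1%. On that scale the 34-per-group design itself has 89.1%, so the two scales should not be mixed. Adding the extra variance from mixing responders and non-responders in the supplement group gives 75.7% by normal approximation.

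**Step 6: separation from the inflation arithmetic.** Dividing by 0.75 gives 34/0.75 = 45.3, so 46 per group. With 46 per group and k = 0, power is still only 80.7%. Correcting the inflation alone would not remove the dilution.

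**The case against.** The strongest reply is that the document never sets up the dilution scenario. It calls the 25% attrition, and the Discussion calls it withdrawal. If those men simply leave without outcomes, power is about 88%, and that small gap comes from multiplying by 1.25 instead of dividing by 0.75. This stands as a limit on size: 78% needs every non-completer to be measured and to gain nothing.

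Second, a man just under the 90% intake threshold may keep most of the benefit, and above about 56% kept the ITT comparison reaches 90% by the protocol's formula. This stands too.

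Third, the planned ANCOVA adjusts for baseline and the sizing formula takes no credit for that. No correlation is given. If it were 0.5 (an assumption), the 78% would become about 88%; at 0.6 it would be about 93%.

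Fourth, the effect comes from a cited trial, and the document does not say whether that estimate already includes non-completers. If it does, applying dilution again would count it twice.

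Fifth, the document does not claim that the 90% is for ITT, and being named first does not make ITT primary. This is correct, but it is also the difficulty: two populations, one power figure, and no statement of which it describes.

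A reader might infer that the ITT analysis has only about 77 to 78% power, or that 90% is out of reach in any scenario. The documents support neither inference, for the reasons above.

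**Conclusion.** The concern holds in a limited form. By the protocol's formula, the 90% describes 34 completers per group at the cited effect. It is not shown for ITT on all 86 men. Nor is it shown for PP under the protocol's own 25% loss, which leaves about 32 per group and about 88%.

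For ITT, the power depends on what happens to the non-completers: about 78% as a lower bound, about 88% if they are all missing, about 89% if they keep half the benefit, and 90% or more above about 56%. These figures assume equal SDs, the implied d of 0.786, the normal approximation and no gain from baseline adjustment. They cannot be narrowed from the document. The weakness is that one unqualified figure stands beside two populations that it does not describe. The trial has not been shown to be badly underpowered.

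**What to change.** In Sample size, state that 90% power refers to 34 completers per group at the effect taken from the cited trial. Add that with 25% lost and no outcomes (about 32 per group) power is about 88%. For ITT, give a range: about 78% if every non-completer is measured with no benefit, rising to 90% or more if they keep most of it. State that no credit is taken for baseline adjustment, and say whether the cited effect already includes non-completers.

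In Statistical analysis, name ITT as the primary population and PP as supportive. Reconcile the exclusion of men taking under 90% of the supplement (Primary aim, Withdrawal of participants and Table 1) with an ITT population of everyone randomised, so that it is clear whether those men's outcomes are collected and analysed.

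The cost is a few sentences and a slightly less favourable stated power. No extra patients are needed.

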### Randomization and blinding

The study randomization procedure will be done by a third person who will not be involved in this study. Each patient will receive a randomization code (determined through a computer-generated schedule). The random permuted blocks (15 blocks of 6) will be used to develop the randomization table. Vitamin D3 or placebo containers will be encoded based on the random codes. The odd and even numbers will be randomly allocated to groups A or B. The containers of vitamin D3 and placebo will be matched in appearance. As the containers will only be labeled with the codes without any further information, the patients will be blind in terms of intervention. The codes related to each group will be opened at the end of the study. In the present study both participants, the researchers and also statistical counselor will be blind in terms of the intervention.

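### The 25% attrition allowance is added to the 34 per group instead of divided out, so 43 per group leaves about 32 completers, not 34, at the planned loss (a minor shortfall)

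*Protocol article*

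**What the plan says.** All of the following is in the protocol article.

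- **Sample size:** "Considering a type I error of 0.05 and 90% for the power study, 34 patients were determined for each group". The next sentence gives the enrolled number: "regarding with the attrition rate of 25%, 43 patients will be included for each group". The sizing variable is the progressive sperm ratio, taken from a cited trial. The means and SDs are not printed. The formula is the usual normal-approximation one for two means, with alpha/2.
- **Primary aim:** high drop-out is expected, and "we would consider a 25% attrition rate for each group of study". The Discussion repeats the 25% as a dropout percentage used in sizing the trial.
- **Study subjects:** the total is 86, which is 43 per group.
- **Withdrawal of participants:** replacement is described only for men who leave before randomisation.

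**The concern.** The section links three figures: 34 completers needed, 25% lost, and 43 enrolled. They do not fit together. If a quarter of 43 men are lost, fewer than 34 are left, so the allowance does not protect the number it was added to protect.

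The protocol treats 25% as its planning value, so this is the expected case and not a pessimistic one. Men lost after randomisation are not replaced under the stated rule, so the gap is not made up later. At stake is the accuracy of the power statement, which readers will use to judge a null result on sperm motility.

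**Working it through.** **Inputs**

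- Needed per group before attrition: 34 (Sample size)
- Type I error 0.05, two-sided because the printed formula uses alpha/2; power 90% (Sample size)
- Attrition: 25% of each group (Primary aim; repeated in the Discussion)
- Enrolled per group: 43 (Sample size); total 86 (Study subjects)
- Means and SDs: not given

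**Step 1. Reproduce the protocol's figure.**
n x (1 + d) = 34 x 1.25 = 42.5, rounded up to **43**. This matches exactly.

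**Step 2. Apply a 25% loss correctly.**
n / (1 - d) = 34 / 0.75 = 45.33, rounded up to **46** per group, or 92 in total. Check: 46 x 0.75 = 34.5, which meets 34, whereas 45 x 0.75 = 33.75 does not. The gap from 43 is 3 per group, 6 in total. Rounding cannot turn 45.33 into 43.

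**Step 3. What 43 per group delivers.**
Completers at 25% loss: 43 x 0.75 = 32.25, about **32**.
Largest loss that still leaves 34: 1 - 34/43 = 0.209, about **21%**.

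**Step 4. Power at 32 per group.**
The raw means and SDs are not needed, because the standardised difference is implied by n = 34 at 90% power. With n = 2(z_alpha/2 + z_beta)^2 / d^2:

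- 2 x (1.960 + 1.2816)^2 = 21.01
- If 34 is exact: d = sqrt(21.01/34) = 0.786
- If 34 was rounded up from just over 33: d = sqrt(21.01/33) = 0.798

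Power = Phi(d x sqrt(n/2) - 1.96), and sqrt(32/2) = 4:

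- d = 0.786: Phi(3.145 - 1.96) = Phi(1.185) = **88.2%**
- d = 0.798: Phi(3.192 - 1.96) = Phi(1.232) = **89.1%**

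The difference detectable with 90% power moves from sqrt(21.01/34) = 0.79 SD to sqrt(21.01/32) = 0.81 SD.

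**Step 5. Check with a t-test.**
Solving for d with the t-test at n = 34 and 90% power gives 0.798. Power at 32 on the same basis is 88.1%, so the answer does not depend on the approximation.

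**The case against.** **The loss is small.** One to two points of power and 0.02 SD in the detectable difference will not decide how the trial is read. This stands, and it sets the weight of the point.

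**The planned analysis may be more efficient than the sizing formula.** Statistical analysis specifies ANCOVA adjusted for baseline. Under the usual variance factor 1 - rho^2, going from 34 to 32 is offset when rho^2 = 1 - 32/34 = 0.059, so rho is about 0.24. The protocol gives no value for rho, so this is an assumption, and the long covariate list costs some degrees of freedom. Even so, a correlation of that size is modest, and the adjustment could recover some or all of the shortfall. It does not correct the stated calculation, which takes no credit for it.

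**The ITT population is all randomised men.** Some men dropped for taking too little supplement may still provide outcomes. Men lost to follow-up would not have the 12-week samples, however. The protocol itself sets 34 as the number needed and adds the allowance to cover men lost, so naming an ITT population does not reconcile 34, 25% and 43.

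**Stronger readings that the documents do not support**

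- A reader might infer that the trial is materially underpowered. Power of about 88 to 89% at the planned loss does not support that.
- A reader might set the 86 men against the randomisation list, "The random permuted blocks (15 blocks of 6) will be used to develop the randomization table", which makes 15 x 6 = 90 codes, and see another contradiction. There is none. Fourteen blocks cover only 84 men, so 15 is the smallest whole number of blocks that covers 86. Spare codes are ordinary, and a final 44:42 split would have a negligible effect on power.
- A reader might put d = 0.786 into a t-test and quote 87.2%. That mixes two methods: on the same basis even 34 completers give only 89.1%, so nearly a point of the apparent loss comes from the approximation and not from attrition.

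**Conclusion.** The point holds as an arithmetic error of minor size. The 43 per group follows from adding 25% to 34. A 25% loss from each group, as the protocol describes it, needs 46. At the planned loss about 32 per group remain, and power on the protocol's own formula is 88.2 to 89.1% against the stated 90%.

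The completer count rests only on printed figures. The power figure rests on two assumptions: that the effect is the one implied by n = 34 with 90% power and two-sided 0.05, and that the loss is equal in both groups. The finding concerns the accuracy of the sample-size statement and gives no reason to doubt that the trial can answer its question.

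**What to change.** Replace the attrition sentence in Sample size with wording such as:

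> 43 per group preserves 34 completers only up to about 21% attrition; at 25% attrition about 32 per group remain and power is about 88%.

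If credit for baseline adjustment is wanted, state the assumed baseline-to-follow-up correlation and its source beside that sentence.

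The cost is one restated figure, slightly less favourable than the present one. No extra patients are needed, and the randomisation list needs no change. Trial time-scale describes enrolment as still open in 2021, with completion predicted for September 2021, so the correction can be made without affecting conduct.
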